#### Randomisation

Upon completing the baseline assessment session, participants are automatically randomised by the computerised system into one of the four experimental conditions in two steps: first, participants are randomised into three main experimental arms (ABM, AppBM, or placebo) with a 1:1:1.25 allocation ratio. Participants assigned to the placebo condition are then further randomised to receive the placebo version of either the AppBM or the ABM training, with a final allocation ratio equal to 1:1:0.62:0.62. Both randomisation steps are stratified by gender (i.e., participants are randomly allocated to one of the conditions to which the fewest participants of their gender have been assigned so far). The two-step randomisation procedure and the uneven ratio over the four experimental conditions were designed to increase the chance of receiving at least one active training intervention, while still allowing for a univocal comparison of each active training module with their respective placebo condition. Allocation concealment is fully ensured, since participant randomisation is fully automated and performed by a computer algorithm.

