Once they complete the study, participants are free to enrol in a second booster training module. Participants assigned to the two placebo conditions are notified with their actual condition assignment and will randomly complete one of the two CBM programmes. Participants assigned to the active training conditions are notified of being part of the approximately 61% of participants who received one of the active interventions and will complete the training module they have not received during the experimental phase.

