### Sample size

A conservative a priori power analysis (G*Power 3.1, open-source software [70]) required a sample size of 114 participants to detect a small-to-medium effect size (Cohen’s *f* = 0.15, equivalent to partial eta squared value of 0.02) for the interaction effect between time and experimental condition for each primary outcome, using mixed ANOVA. Power of 0.80, Bonferroni-adjusted type-I error probability of 0.025 (0.05/2 primary outcomes) and moderate correlation between the repeated measures of 0.3 were assumed. Based on a similar online CBM study for alcohol drinking problems [42], an additional 60% dropout rate at follow up was taken into account, leading to a final target sample size of 182 participants.

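### The gender-stratified rule described for step one of the randomisation gives 1:1:1, not the stated 1:1:1.25

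*Protocol article*

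**What the plan says.** The Randomisation section describes two automated steps after the baseline session.

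- **Step one.** Participants are "randomised into three main experimental arms (ABM, AppBM, or placebo) with a 1:1:1.25 allocation ratio".
- **Step two.** Those in the placebo arm are randomised again to one of the two placebo versions, "with a final allocation ratio equal to 1:1:0.62:0.62".
- **Rule for both steps.** "Both randomisation steps are stratified by gender", and a parenthesis introduced by 'i.e.' explains this: "participants are randomly allocated to one of the conditions to which the fewest participants of their gender have been assigned so far".
- **Purpose.** The procedure and "the uneven ratio over the four experimental conditions were designed to increase the chance of receiving at least one active training intervention".

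Two other places bear on the point. Participants and procedure says that people in the active arms who go on to the booster module are told they belong to the "approximately 61% of participants who received one of the active interventions". Sample size gives the total, "leading to a final target sample size of 182 participants".

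**The concern.** A rule that always picks the least-filled condition pulls the conditions to equal size. If placebo is to hold 1.25 participants for each one in an active arm, the rule must compare counts after dividing by the target weights, or use unequal probabilities. The parenthesis mentions neither, so as written the 1.25 plays no part in the assignment.

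Three things are at stake:

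- the size of each placebo group, which is the smaller side of each primary comparison;
- the accuracy of the percentage given to participants in the active arms;
- whether a reader can reproduce how the allocation sequence was generated.

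**Working it through.** **Inputs.** Step-one weights 1:1:1.25, final ratio 1:1:0.62:0.62 and the fewest-so-far rule (Randomisation); about 61% active (Participants and procedure); N = 182 (Sample size). The gender mix is not given. Two gender strata are assumed, with 50%, 80% or 95% in one of them.

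**1. The stated figures agree with one another.**
- Placebo half: 1.25/2 = 0.625, given as 0.62.
- Active share: 2/3.25 = 61.5% (2/3.24 = 61.7% with the rounded ratio), given as about 61%.
- Arm sizes: 182 × 1/3.25 = 56 for each active arm; 182 × 1.25/3.25 = 70 for placebo, or 35 for each version.

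**2. The rule as written, on unweighted counts over three arms.** Within a gender, no arm can get more than one participant ahead of another.
- Expected size: 182/3 = 60.7 for each arm, and 182/6 = 30.3 for each placebo version.
- Active share: 2/3 = 66.7%.
- Range for placebo: 182 = 3 × 60 + 2, so the two gender totals leave remainders on division by 3 of (1,1), (2,0) or (0,2). Total placebo is therefore between 60 and 62 whatever the gender mix. The target of 70 cannot be reached.

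A simulation with 4,000 runs per gender mix and ties broken at random agrees: mean sizes 60.7/60.7/60.7, placebo split 30.3/30.3, placebo-to-active ratio 0.98 to 1.03, and placebo never above 62.

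**3. Other readings, same simulation.**

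| Reading of the rule | ABM / AppBM / placebo | Placebo split | Active share |
|---|---|---|---|
| Unweighted, three arms, then two versions | 60.7 / 60.7 / 60.7 | 30.3 / 30.3 | 66.7% |
| Unweighted, all four conditions at once | 45.5 / 45.5 / 91.0 | 45.5 / 45.5 | 50% |
| Counts divided by 1, 1, 1.25, then two versions | 56.1 / 56.1 / 69.8 | 34.9 / 34.9 | 61.6% |

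Only the third recovers the stated ratio and the 61%, and its weighting is not in the text.

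**4. Effect on precision if the unweighted rule ran.** The variance of an active-placebo contrast is proportional to 1/n(active) + 1/n(placebo), taking equal outcome variance in both groups.
- Stated ratio: 1/56 + 1/35 = 8.45/182 = 0.04643.
- Rule as written: 3/182 + 6/182 = 9/182 = 0.04945.
- Variance ratio: 9/8.45 = 1.065. Standard-error ratio: √1.065 = 1.032.

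The total per comparison is the same, 56 + 35 = 91 and 60.7 + 30.3 = 91, so the loss comes from imbalance alone. The variance ratio is unchanged by attrition if retention is equal across arms.

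**The case against.** The best defence is that the parenthesis only glosses what stratified by gender means and does not set out the full algorithm. It never says the counts are unweighted. It follows directly on the two ratios, and the 61% agrees with them. Read with the ratio in mind, fewest can mean fewest relative to target, and that reading reproduces every figure. An article may also leave such detail to a fuller protocol.

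Much of this stands. The rule's wording is the likelier slip, and the intended ratio is not in doubt. But the article does not leave the algorithm out; it states one, and that one does not deliver the ratio beside it. The weighted reading has to be supplied by the reader. The stated purpose does not settle the matter either, since 1:1:0.5:0.5 is also uneven and also favours active training.

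Three stronger inferences are tempting but unsupported.

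- **That the trial actually allocated 1:1:1.** No accrued counts or code are shown.
- **That a least-filled rule makes assignments predictable and so threatens concealment.** Allocation is fully automated, and both participants and investigators are described as unaware of condition. The article identifies nobody who could see and exploit the sequence.
- **That a wrong 61% could influence outcomes.** It is disclosed only after participants complete the study.

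**Conclusion.** The description of step one contradicts itself: the stated rule yields 1:1:1 and the stated ratio is 1:1:1.25. The gap is about nine placebo participants in 182 (70 against 60.7) and about five percentage points in the active share (61.5% against 66.7%). Step two is consistent, because the same rule gives the intended equal split there. The result rests on reading the counts as unweighted and on two gender strata; the gender mix makes no difference.

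If the unweighted rule ran, the cost is modest: about 6.5% more variance and about 3% more standard error for each contrast. There is no bias, because each active arm is still compared with its own randomised placebo. If the weighted rule ran, only the description is wrong. One of the two statements needs correcting in either case.

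**What to change.** Have the IT department member who independently handles data storage (Blinding section) check the platform code and the accrued counts by arm and gender, and report which rule is running without unblinding the investigators.

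- **If counts are weighted by the target ratio:** amend the sentence to say that step one picks the arm with the fewest participants of that gender relative to 1:1:1.25, and that step two uses equal weights.
- **If unweighted counts were used:** change the stated ratio to 1:1:0.5:0.5, the implied arm sizes to about 61:61:30:30 and the 61% to about 67%, and report the realised allocation.

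In the second case, do not simply switch to weighted cumulative counts. According to Trial status, recruitment has been open since February 2015. A catch-up rule would send late entrants disproportionately to placebo and so link arm to calendar time, which the analysis would have to take into account. Under Study design, a major procedural change would also go to the ethics committees.

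The cost is one code check and a short correction of text. Participants already allocated are not affected.

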#### Blinding

Since the study procedure is fully automated, with all training and assessment sessions fully delivered online, both the participants and the investigators are not aware of which experimental condition participants are assigned to. To prevent participants from guessing the training intervention they receive, they are required to respond to an irrelevant feature in all training paradigms (e.g., the orientation of the picture or probe) instead of reacting to the content of picture (gambling or non-gambling) [32, 34, 35, 44]. To also guarantee full blinding during data analyses, the dataset for the outcome analyses will be retrieved from the online platform in anonymised format only at conclusion of the data collection. Accurate storage and back-up of all collected data is independently handled by a member of the information technology (IT) department.

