#### Data management

Participants create their personal research account at registration on the study online platform and can login from their own computer whenever and wherever they wish. Participant data are anonymised via the assignment of a four-digit user-ID number. Online data handling and storage conform to requirements of EU legislation on data protection: communication between project servers and devices used by participants or researchers for conducting, managing, or taking part in the study is encrypted through Secure Sockets Layer (SSL) encryption technology and databases are maintained securely behind a firewall. All core technologies, such as database, web-server, server-side and client-side frameworks are regularly inspected and updated. Sensitive data (such as participant task results) are stored in databases that are separate from those storing personally identifiable data (such as username, password, email address, if any). The two databases are running on different machines managed by different system administrators and institutions (University of Amsterdam and Qualtrics). Hence, multiple systems need to be breached in order to obtain sensitive data and link these to an individual. Finally, complete confidentiality applies to all data, and any data used for post-study analyses are anonymised.

The RCT does not include a data monitoring committee. Data collection and participants’ process along the study sessions is regularly monitored by two of the primary investigators with the support of the IT department through inspection of the activity logs on the online platform. The inspections are mainly in order to detect and solve any technical problem with the online system and monitoring participants’ inclusion rate and adherence to the study procedures. Since the launch of the study, yearly review meetings with all primary investigators have been scheduled independently from the study sponsor in order to evaluate and discuss the trial progress, with a special focus on participants’ recruitment and drop-out rates. At conclusion of the data collection, all primary investigators will have access to the final trial dataset independently from the sponsor organisation and without any type of limitation.

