### Data analysis

Multiple imputation of missing data will be performed for intention-to-treat analyses. Before running all analyses, all variable distributions will be screened for normality assumptions and univariate outliers. The use of parametric or non-parametric statistical tests will be adjusted accordingly. Each training group will be compared to its control group to check for any baseline difference in demographics (e.g., age and gender), severity of gambling problems (SOGS), and alcohol use. When significant differences are found and the relevant baseline variables also correlate with the outcomes of interest, they will be added as covariates in subsequent analyses.

Changes in gambling frequency and expenditure from baseline to the 6-month follow up will be examined through two separate 2 (condition: active training vs. placebo) × 4 (time: baseline, post-intervention, 3-month and 6-month follow up) mixed analysis of variance (ANOVA) analyses, one per training module. Each CBM condition is contrasted against its control condition, with the baseline assessment as reference time point for the following time points.

Changes in gambling cognitive biases as a result of each CBM intervention will be explored with a 3 (time: baseline, post-intervention, 3-month follow up) × 2 (condition: active vs. placebo training) × 2 (stimulus category: gambling vs. control) mixed ANOVA for approach bias (i.e., AAT task) and a 3 (time: baseline, post-intervention, 3-month follow up) × 2 (condition: active vs. placebo training) × 2 (trial type: on top vs. after) mixed ANOVA for attentional bias (i.e., VPT task). Any change in depression symptoms and gambling problems would be explored using two 2 (condition: active vs. placebo training) × 4 (time: baseline, post-intervention, 3-month and 6-month follow-up) mixed ANOVA analyses, one per training module.

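### Anonymised, late data retrieval does not deliver the blinded analysis the protocol says it guarantees: it hides identity, not condition, and the unequal allocation would expose the active group even under neutral codes

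*Protocol article*

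**What the plan says.** The protocol article's Blinding section covers participants and investigators during conduct and then adds a safeguard for the analysis stage. Its stated purpose is "To also guarantee full blinding during data analyses", and the means are that "the dataset for the outcome analyses will be retrieved from the online platform in anonymised format only at conclusion of the data collection". The IT department's role there is independent storage and back-up.

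The Data management section says what anonymised means: "Participant data are anonymised via the assignment of a four-digit user-ID number". It also gives all primary investigators unrestricted access to the final dataset once data collection ends.

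The Randomisation section describes participants as "randomised into three main experimental arms (ABM, AppBM, or placebo) with a 1:1:1.25 allocation ratio", with placebo then split between the two modules, "with a final allocation ratio equal to 1:1:0.62:0.62".

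The Data analysis section screens distributions and outliers first, and then "The use of parametric or non-parametric statistical tests will be adjusted accordingly". It next compares each training group with its own control at baseline. A variable that differs significantly and also correlates with the outcome is added as a covariate.

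**The concern.** The article states a property, full blinding of the analysis, and names the procedure meant to produce it. That procedure has two parts, and neither conceals condition. Replacing identity with a user-ID leaves the condition variable untouched. Waiting until data collection has ended removes the opportunity for interim looks, but the analysis begins after that point. The article mentions no withheld condition variable, masked coding or independent analyst.

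This matters because delivery and assessment are automated, so the analysis is the main stage at which an investigator's discretion can enter. Some discretion is left there: the choice of test follows a look at the distributions, and covariates are selected after a look at group differences and outcome correlations. A reader of a trial labelled double-blind would credit it with a protection at this stage that the described steps do not supply.

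**Working it through.** **1. The plan's own figure.** With the first-step ratio 1:1:1.25, the share on active training is 2/(1 + 1 + 1.25) = 2/3.25 = 61.5%. With the rounded final ratio it is 2/(1 + 1 + 0.62 + 0.62) = 2/3.24 = 61.7%. Both agree with the statement in Participants and procedure, "approximately 61% of participants who received one of the active interventions". The placebo split is 1.25/2 = 0.625, given as 0.62.

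**2. Expected group sizes.** Sample size gives a target of 182.
- Each active arm: 182/3.25 = 56.
- Placebo in total: 56 × 1.25 = 70; per module: 70/2 = 35.
- Ratio within a module: 56/35 = 1.6.

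**3. Would neutral codes hide the active group?** They would fail if the larger group of a pair is nearly always the active one. The probability of that was simulated.

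| Setting | Group sizes, active vs placebo | Larger group is active |
|---|---|---|
| Least-filled allocation within gender, targets 1:1:1.25 | 55–57 vs 34–36 | 100% of 1,000 simulated trials |
| Least-filled rule taken literally (equal targets for three arms) | about 61 vs 30 | 100% of 1,000 simulated trials |
| Simple randomisation | expected 56 vs 35 | 0.985 per pair; 0.970 for both pairs |
| Only the 40% who complete are visible (0.4 × 182 ≈ 73) | – | about 0.91–0.95 per pair; 0.997 on the literal reading |

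The least-filled rows follow the Randomisation text, in which participants are "randomly allocated to one of the conditions to which the fewest participants of their gender have been assigned so far". They assume 20% of participants in the smaller gender stratum, a share the article does not give. The last row applies the 60% attrition named in Data analysis equally to all arms. The intention-to-treat set with multiple imputation keeps the full group sizes, so the first three rows are the relevant ones for it.

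**4. Which analysis decisions need group labels?**
- *Covariate selection:* yes. It compares each training group with its control, so a group column must be present, and by step 3 its sizes show which group is active. The same rule also uses outcome correlations.
- *Outlier and normality screening, and the choice of test family:* not necessarily. These can be done on pooled data, but the article does not say that they will be.
- *Imputation:* the article says only that multiple imputation will be performed. Nothing indicates that the model is chosen after the data are seen.

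**The case against.** The strongest reply is that holding and releasing condition codes is data-management or analysis-plan detail, which an article commonly leaves out, and that the user-ID is described as a privacy measure rather than as everything done to the export. This would be a full answer if the article were silent. It is not: it asserts a guarantee and names the means, and those means do not produce it.

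A second reply is that the group-size argument rebuts a safeguard the article never offers. If no condition variable is supplied at first, the ratio reveals nothing; if labelled data are supplied, the ratio is irrelevant. This is correct. The ratio matters only for the natural repair of coding the arms neutrally, and shows that this alone would not be enough.

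Third, the covariate choice is largely rule-driven, with gambling severity and alcohol use named. That stands in part, but the demographic variables are given only as examples, so some discretion remains.

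Fourth, a reader might infer that all the data-driven choices would be made unblinded, or that training-block trials in the dataset would give condition away because active training shows only some trial types. The article supports neither. Screening and test choice can be done without labels, and nothing says that training-block trials are part of the outcome dataset; the bias scores come from assessment versions in which trial types are balanced in every arm.

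**Conclusion.** The claim of full blinding during data analyses is not supported by the procedure described. With about 56 active and 35 placebo participants per module, the active group would be identifiable from size alone with probability 0.985 per pair under simple randomisation, and in every simulated trial under the least-filled rule. Covariate selection as written would therefore be made with the active group identifiable. For outlier handling and test family, unblinded choice is possible but not established.

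These probabilities say how often the active group could be recognised. They do not measure bias in any result, and none has been shown. Participant blinding, automated allocation, automated outcome collection and the absence of interim analyses are unaffected, and the article calls the study strictly explorative. The conclusion rests on the article alone: a fuller document may describe withheld condition data, in which case the Blinding section should say so. The point should be corrected, but it does not invalidate the trial.

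**What to change.** Rewrite the analysis part of the Blinding section as a two-step release through the IT department, which already stores the data independently.

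1. Release the outcome dataset without the condition variable and without any training-block trial data. On these pooled data, decide and date the outlier handling, the test or transformation, and the covariate set. Covariates need explicit treatment, because the present rule cannot be applied without labels. Either choose them by pooled correlation with the outcome, or fix a closed list and a mechanical rule at this step, so that nothing is left to judgement after release.
2. Release condition and run the locked analysis.

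The Data management statement on unrestricted investigator access should then be worded to apply after step 2, and the covariate sentence in Data analysis brought into line.

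If this is not wanted, delete the claim of full blinding during data analyses and keep the statements about conduct.

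The first option costs one extra data export and a short dated record; the second costs one sentence. Neither changes the design or the sample size.

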#### Data management

Participants create their personal research account at registration on the study online platform and can login from their own computer whenever and wherever they wish. Participant data are anonymised via the assignment of a four-digit user-ID number. Online data handling and storage conform to requirements of EU legislation on data protection: communication between project servers and devices used by participants or researchers for conducting, managing, or taking part in the study is encrypted through Secure Sockets Layer (SSL) encryption technology and databases are maintained securely behind a firewall. All core technologies, such as database, web-server, server-side and client-side frameworks are regularly inspected and updated. Sensitive data (such as participant task results) are stored in databases that are separate from those storing personally identifiable data (such as username, password, email address, if any). The two databases are running on different machines managed by different system administrators and institutions (University of Amsterdam and Qualtrics). Hence, multiple systems need to be breached in order to obtain sensitive data and link these to an individual. Finally, complete confidentiality applies to all data, and any data used for post-study analyses are anonymised.

The RCT does not include a data monitoring committee. Data collection and participants’ process along the study sessions is regularly monitored by two of the primary investigators with the support of the IT department through inspection of the activity logs on the online platform. The inspections are mainly in order to detect and solve any technical problem with the online system and monitoring participants’ inclusion rate and adherence to the study procedures. Since the launch of the study, yearly review meetings with all primary investigators have been scheduled independently from the study sponsor in order to evaluate and discuss the trial progress, with a special focus on participants’ recruitment and drop-out rates. At conclusion of the data collection, all primary investigators will have access to the final trial dataset independently from the sponsor organisation and without any type of limitation.

